### Process evaluation

It is essential for credibility that researchers acquire information about the quality of an intervention and its implementation in a given study [46, 47]. Leontjevas et al. (2012) proposed a process evaluation model based on first- and second-order data, which we will adopt in this study. The first-order data provide information about the internal and external validity, comprising of the sample quality (e.g., recruitment, randomization, and reach) and the intervention quality (e.g., relevance, feasibility, and extent to which an intervention was performed). The second-order data are then examined (implementation knowledge), such as implementation components that were delivered and received and the barriers to, and facilitators of, implementation. The internal project leader and coach will each receive a digital questionnaire to assess these aspects. We will follow this up with a semi-structured telephone interview to address ambiguities and to seek additional comments.

### Measurements

An overview of the outcomes and measurement instruments is provided in Table 2. Demographic data will be extracted from medical files by the researchers, including residents’ age, sex, type of dementia, pro re nata psychotropic drug use, date of last medication review, and date of admission to the DSCU. Cognitive abilities will be examined using the Cognitive Performance Scale (CPS), a reliable and valid scale that rates cognition, communication, activities of daily living and consciousness from 0 (intact) to 6 (very severe impairment) [48]. The instrument has a sensitivity and specificity of 0.94 and has been validated against the Mini Mental State Examination [49]. The CPS will be used by nursing staff, on paper, in the presence of a researcher.

**Table 2 Tab2:** Overview of the measurement instruments

*Variable*	*Measurement instrument*	*Outcome measure*	*Problem analysis/ feedback MPT*
Inappropriate psychotropic drug use	APID	Primary outcome	Problem analysis + feedback 8 and 16 months ^a^
Frequency psychotropic drug use	Retrieval from medical records	Secondary outcome	Problem analysis + feedback 8 and 16 months ^a^
NPS	NPI-NH	Secondary outcome	–
	CMAI		Problem analysis
QoL	EQ-VAS ^b^	Secondary outcome	Problem analysis
	RISE		–
Current difficulties managing NPS; *NH staff*	Self-designed questionnaire [digital] + semi-structured interviews for NH staff	–	Problem analysis
Current status of managing NPS and quality of care; *relatives*	Self-designed questionnaire for relatives	–	Problem analysis
Attitude toward new interventions	EBPAS [digital] ^c^	Process evaluation	Problem analysis
Organizational culture	Questionnaire [digital] *CVF scale for long-term care* ^c^	Process evaluation	Problem analysis
Process evaluation data *model of Leontjevas* et al.*, 2012*	Self-designed questionnaire [digital] + semi-structured interview internal project leader and coach	Process evaluation	–

^a^NHs who start as an intervention group receive information on psychotropic drug use at the beginning (problem assessment), 8 months (interim results) and 16 months. NHs who start as a deferred intervention group receive information on psychotropic drug use at 8- (problem assessment) and 16 months

^b^EQ-VAS is administered to both nursing staff and relatives, at each measurement (0, 8, 16 months)

^c^The EBPAS + organization culture questionnaires are administered in the context of the problem assessment at 0 months (start intervention group) or 8 months (start deferred intervention group), as well as at 16 months in the context of the process evaluation

Abbreviations: *APID* Appropriateness of Psychotropic Prescription In Dementia, *CMAI* Cohen–Mansfield Agitation Inventory, *CPS* Cognitive Performance Scale, *CVF* Competing Values Framework, *EBPAS* Evidence-Based Practice Attitude Scale, *MPT* Multidisciplinary project team, *NPS* neuropsychiatric symptoms, *NH* Nursing homes, *NPI-NH* Neuropsychiatric Inventory-Nursing Home, *QoL* Quality of Life, *RISE* Revised Index of Social Engagement, *VAS* Visual analog scale

### Primary outcome

Psychotropic drugs will be categorized according to the Anatomical Therapeutic Chemical (ATC) classification [50]. The primary outcome is the appropriateness of psychotropic drug use, and this will be measured with the Appropriateness of Psychotropic drug use In Dementia (APID) index [23]. This index rates the prescription of regular psychotropic drugs for NPS in people with dementia, including antipsychotic, anxiolytic, hypnotic, antidepressant, anticonvulsant, and anti-dementia drugs. Psychotropic drugs administered for dementia, sleep disturbance, and delirium will be scored with the APID index, but those prescribed for psychiatric disorders will not be scored. Treatment appropriateness will be measured on seven domains: indication, evaluation, dosage, drug-drug interactions, drug-disease interactions, duplications, and therapy duration. For each domain, a score between zero (appropriate) and two (inappropriate) can be given, allowing an overall appropriateness score to be calculated (weighted sum score). The APID has been validated in residents of DSCUs in the Netherlands (intraclass correlation coefficient, 0.577–1.000) [23]. The researchers will extract information on psychotropic drug prescribing from medical records.

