In recent decades, a number of multidisciplinary care programs have been developed to target the factors associated with inappropriate prescribing and/or to shift practice toward a greater use of non-pharmacological interventions (e.g., STA-OP, GRIP, PROPER, AiD, Dementia Care Mapping, RedUSe, and TIME) [28–34]. RedUSe is a good example of a multi-strategic interdisciplinary intervention that took place in 150 residential aged care facilities and was shown to reduce antipsychotic prescribing by 13% and benzodiazepine prescribing by 21%, without increasing their pro re nata use. Although this showed that such an intervention can be successful [34], it is generally the case that the effects of these multidisciplinary care programs or interventions are variable. In the GRIP study, for example, the effects of a multidisciplinary care program for challenging behavior were considered small, probably due to suboptimal implementation. Adjusted analyses showed larger effects in Dementia Specialized Care Units (DSCUs), in which implementation was good [29]. The results of a successful and widely implemented person-centered care approach in the United Kingdom have not been replicated in German NHs [35]. Although several changes were made to the intervention, it was thought that implementation barriers caused the loss of effect between populations. In other research, Grimshaw et al. stated that implementation studies seeking to change professional behavior achieve an effect size of 10 to 20%, with the effects likely related to the degree to which underlying barriers are addressed [36]. Striving for any culture change is challenging and takes time, and it might be unrealistic to expect larger effects. However, it is documented that a lack of effect may reflect a failure of implementation rather than a failure of the intervention itself [37, 38].

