### Study population and recruitment

NHs will be recruited by organizing a national kick-off and using media channels to gain attention. Any interested NHs in the Netherlands can apply to participate and will be considered eligible if the board of directors and the client council agree to participate and are prepared to invest the requisite time. We will exclude NHs in which major organizational changes are expected during the study period or if other projects related to psychotropic drug use are currently running.

The study population will comprise residents with dementia who reside in psychogeriatric units (e.g., DSCUs). NHs can have several DSCUs, and several DSCUs from one NH can participate. However, DSCUs designed to deliver care for residents with Korsakov syndrome, acquired brain injury, Down syndrome, or young-onset dementia will be excluded. Although interventions will be aimed at the DSCU level, we will still need to gather data on residents to assess outcomes. Residents will be eligible to participate if they have a diagnosis of dementia according to the Diagnostic and Statistical Manual of Mental Disorders (fifth edition), have a life expectancy of at least 3 months, as judged by a physician, and provide written informed consent. We will also include users and nonusers of psychotropic drugs. It is anticipated that most residents will be at an advanced stage of dementia and may be mentally incompetent. The physician of the relevant DSCU will therefore be asked to assess a resident’s mental competence to provide informed consent. If they are not deemed competent, an employer of the registry office at each NH will send the informed consent form to a residents’ legal representative. In the absence of a response, a reminder request to return the informed consent form will be made once. If no response will be obtained, residents will not be included.

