### Secondary outcomes

The secondary outcomes will be the frequency of psychotropic drug use, the frequency of NPS, and the QoL. The frequency of psychotropic drug use will be extracted by the researchers from medical files, and NPS and QoL will be assessed by nursing staff on paper, in the presence of a researcher. Proxy measures of NPS and QoL (nurse assessments) will be used on the assumption that residents lack capacity. NPS will be measured with the NPI-NH and the Cohen–Mansfield Agitation Inventory (CMAI). QoL will be measured using the visual analog scale (VAS) of the EQ. 5D (i.e., the EQ-VAS).

The NPI-NH measures the prevalence, frequency, severity, and associated caregiver distress of 12 neuropsychiatric symptoms. All symptoms are rated on Likert-type scales, with four-point scales used for frequency, three-point scales used for severity, and six-point scales used for caregiver distress. When a symptom is not present, the frequency, severity, and caregiver distress are not scored [51]. We plan to use the Dutch version of the NPI-NH, which has demonstrated high inter-rater agreement and validity as a rating scale [52].

The CMAI is the most used tool for determining the frequency of agitation and aggression [53]. The CMAI consists of 29 items, subdivided into three subscales: physical aggression, physically nonaggressive behavior, and verbally agitated behavior. Scores are rated on seven-point Likert-type scales, rating symptoms over the preceding 2 weeks from “never” to “several times an hour” [54]. The translated and validated Dutch version by De Jonghe and Kat (1996) will be used, which has established reliability (Cronbach’s α = 0.82) and construct validity (Inter-rater agreement = 0.89) [55–57].

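### The APID rates regular prescriptions only, and no stated outcome clearly captures a switch from regular to as-needed (PRN) psychotropic use

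*Protocol article*

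**What the plan says.** The Primary outcome section limits the score by type of prescription: "This index rates the prescription of regular psychotropic drugs for NPS in people with dementia". Each of seven domains is rated from 0 to 2 and a weighted sum is formed. The article does not say how several drugs in one resident are combined, or what value a resident with no scored drug receives.

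PRN data are mentioned once in the trial's own methods. The Measurements section lists them as demographic data from the medical files, after age and sex: "type of dementia, pro re nata psychotropic drug use, date of last medication review, and date of admission to the DSCU".

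The outcomes beside the APID are listed as follows: "The secondary outcomes will be the frequency of psychotropic drug use, the frequency of NPS, and the QoL". On the source of the first of these, the Secondary outcomes section adds: "The frequency of psychotropic drug use will be extracted by the researchers from medical files". Neither that section nor Table 2 says whether PRN drugs are counted. The Data analysis section describes no analysis of PRN use.

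The Background describes an earlier multi-strategic programme that lowered antipsychotic and benzodiazepine prescribing "without increasing their pro re nata use".

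On who is studied, the Study population and recruitment section says: "We will also include users and nonusers of psychotropic drugs". The Sample size section counts only users of psychotropic drugs when it derives the required number.

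**The concern.** A drug changed from regular to PRN is no longer rated by the APID, although the resident may still receive it. On the primary outcome such a change cannot be told apart from a true stop. Nothing else in the stated outcome set is certain to show the difference.

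This matters because the arms are exposed differently. Staff and researchers know the allocation. Table 2, note a, gives the intervention homes information on psychotropic drug use at the start, and the deferred homes get theirs only at 8 months. In Period 1 the intervention homes also have a coach and a plan that the researchers check for its aim of reducing inappropriate use. Switching could therefore be more common in one arm. If so, part of the APID contrast would reflect a change in the form of the prescription. The article reports on PRN use when it describes the earlier programme, but does not commit this trial to the same check.

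**Working it through.** **1. The plan's own figures.** From the Sample size section: difference 5, SD 15, power 0.80, alpha 0.05 (taken as two-sided), 25 residents per home, intraclass correlation 0.1.

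- Per arm: 2 × (1.960 + 0.842)² × 15² / 5² = 141.3, rounded up to 142, so 284 users in total, as stated.
- Design factor, from the stepped-wedge formula with 2 steps, 1 baseline and 1 measurement per step: [1 + 0.1 × (50 + 25 − 1)] / [1 + 0.1 × (25 + 25 − 1)] × [3 × 0.9 / (2 × (2 − 0.5))] = (8.4 / 5.9) × 0.9 = 1.281, as stated (1.28).
- 284 × 1.28 = 363.5, so 364; 364 / 0.60 = 606.7, so 607, as stated.

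No sample-size figure is disputed. The point concerns what the outcome measures.

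**2. What switching does to the score.** Two inputs are not in the documents: the mean APID score and the handling of a resident with no scored drug. I therefore take both branches.

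*Branch A (assumption: the score becomes 0).* Let m be the mean score and f the excess share of users in the intervention arm, over control, whose scored drugs are all switched. If switchers have average scores, the apparent fall is f × m, so creating the whole 5-point target needs f = 5/m.

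| Assumed m (scale 0 to 102.8) | f needed for 5 points | Apparent fall at f = 10% |
|---|---|---|
| 10 | 50% | 1 point |
| 20 | 25% | 2 points |
| 30 | 16.7% | 3 points |
| 40 | 12.5% | 4 points |
| 50 | 10% | 5 points |

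*Branch B (assumption: the resident leaves a users-only analysis).* No 0 is credited. If switchers score d points above those who stay, the mean of the remaining users moves by −f × d. At f = 10%:

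| d | Shift in the mean of remaining users |
|---|---|
| −10 | +1 |
| 0 | 0 |
| +10 | −1 |
| +20 | −2 |

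The shift can look favourable, neutral or unfavourable. On the 284 basis, losing 10% of one arm lowers power from 0.80 to about 0.78, and losing 20% to about 0.75. The larger issue in this branch is selection after randomisation on something that the intervention may affect.

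**The case against.** A reader might infer that every switch counts as success in the primary outcome. The article does not support that. It needs a rule that an unscored drug gives 0, or that scores are added over a resident's drugs, and neither is stated. Other places point elsewhere: the sample size is built on users, and the Background cites appropriateness as a share of prescriptions. Under such an analysis the direction is open, as branch B shows. This objection stands in full.

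A reader might also infer that the trial makes no check on PRN use at all. The frequency outcome comes from the same medical files and, unlike the APID, is not restricted to regular drugs. It may already count PRN use. Its operational definition may sit in a full protocol or SAP that is not shown. This also stands, so the claim is limited to no stated outcome *clearly* covering the switch.

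The mechanism must not be overdrawn either. Homes choose their own interventions, medication review is only one option, and the aim is less inappropriate prescribing, not less regular prescribing. The 8-month feedback comes after the 8-month measurement, so it cannot affect the comparison over the first period. What remains is enough for switching to differ by arm: start-of-study information and coaching in one arm only, without blinding. The documents do not show that it will.

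Finally, no mean score and no switching rate are given, so branch A is arithmetic and says nothing about likelihood. The low end, where half of all users would have to switch, is implausible as a full explanation.

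The objections do not remove the gap itself. The list of outcomes is protocol content. The article sets it out in Table 2 and the outcome sections, and PRN use is not in it.

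**Conclusion.** The point holds in a limited form. The primary outcome does not capture regular-to-PRN switching, and no stated outcome clearly does. If switching differs by arm, the APID contrast is distorted: toward benefit if an unscored drug counts as 0, in an unknown direction if the resident drops out of a users-only analysis. The size cannot be derived from the documents. Under the score-0 assumption, an excess of 10% of users switching would give 1 to 5 points for m between 10 and 50, against a target of 5. A demonstrated bias in favour of the intervention should not be claimed. This is a cheap improvement that would let the trial say whether a fall in APID came with a rise in PRN use.

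**What to change.** 1. Move PRN psychotropic use from the demographic list to a named secondary outcome. Extract it at 0, 8 and 16 months and compare the arms with the same multilevel model as the other outcomes.
2. In the frequency outcome, count regular and PRN use separately.
3. Add a sensitivity analysis of the APID in which a regular-to-PRN switch is not credited as improvement: a drug that was regular at the previous wave and is PRN now keeps its previous score. Limit it to residents with a previous-wave score. Newly admitted residents who replace those lost have none, so item 1 carries most of the weight.
4. Report that analysis beside the primary result. It should not be a condition for the conclusion.

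The cost is a little more extraction from files that are already opened at each wave, one more outcome line and one more analysis. The headline estimate may turn out less favourable. Nothing here judges whether PRN prescribing is clinically right or wrong.

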### Secondary outcomes

The secondary outcomes will be the frequency of psychotropic drug use, the frequency of NPS, and the QoL. The frequency of psychotropic drug use will be extracted by the researchers from medical files, and NPS and QoL will be assessed by nursing staff on paper, in the presence of a researcher. Proxy measures of NPS and QoL (nurse assessments) will be used on the assumption that residents lack capacity. NPS will be measured with the NPI-NH and the Cohen–Mansfield Agitation Inventory (CMAI). QoL will be measured using the visual analog scale (VAS) of the EQ. 5D (i.e., the EQ-VAS).

The NPI-NH measures the prevalence, frequency, severity, and associated caregiver distress of 12 neuropsychiatric symptoms. All symptoms are rated on Likert-type scales, with four-point scales used for frequency, three-point scales used for severity, and six-point scales used for caregiver distress. When a symptom is not present, the frequency, severity, and caregiver distress are not scored [51]. We plan to use the Dutch version of the NPI-NH, which has demonstrated high inter-rater agreement and validity as a rating scale [52].

The CMAI is the most used tool for determining the frequency of agitation and aggression [53]. The CMAI consists of 29 items, subdivided into three subscales: physical aggression, physically nonaggressive behavior, and verbally agitated behavior. Scores are rated on seven-point Likert-type scales, rating symptoms over the preceding 2 weeks from “never” to “several times an hour” [54]. The translated and validated Dutch version by De Jonghe and Kat (1996) will be used, which has established reliability (Cronbach’s α = 0.82) and construct validity (Inter-rater agreement = 0.89) [55–57].

The EQ-VAS records a respondent’s self-rated health on a vertical scale ranging from “best imaginable health state” to “worst imaginable health state” [58]. In our study, we will use the two proxy-versions of the EQ-VAS reported in a previous Dutch study [59]. Nursing staff and family members will be asked to rate the residents’ QoL and health status, both from their own perspective and from the perspective of the resident. In addition, the social engagement of residents will be measured as an important proxy of QoL, using the Revised Index of Social Engagement (RISE) [60]. The RISE is part of the inter-RAI Long-Term Care Facilities Assessment System and consists of six dichotomous items related to social behavior [61–63]. Its reported reliability and validity are considered sufficient [60].

### Measurements problem assessment

We will gather information on inappropriate psychotropic drug prescribing, frequency of psychotropic drug use, NPS frequency, and QoL. Also, we will analyze current difficulties in managing NPS using a self-designed, digital questionnaire for NH staff (i.e., physicians, psychologists, and nurses) to assess the following: (1) the detection, analysis, treatment, and evaluation of NPS, and (2), efforts to prevent NPS, any views about NPS, and the presence of multidisciplinary cooperation. The questionnaire will not be used to measure an outcome; instead, it will only be used to examine problems that NH staff perceive when dealing with NPS and inappropriate psychotropic drug prescribing. Scores will be rated on four-point Likert-type scales ranging from “never/rarely” to “at all times” for the frequency measure, and from “not satisfied” to “very satisfied” for the extent of satisfaction. The questionnaire has been piloted in two NHs and adjusted based on user experiences.

To gain a more in-depth insight into the processes that play a role in managing NPS and the prescription of psychotropic drugs, researchers ([name], [name]) will conduct several semi-structured interviews with members of the MPT (e.g., physicians, psychologists, nursing staff, and managers). Several interviews were trialed in a pilot study at two NHs, and the interview formats have been adjusted according to user experience.

We also plan to address the attitudes of health care staff toward the use of new interventions or treatments. Values and beliefs on these issues influence the degree to which innovations are initiated and implemented in clinical practice [64–66], and considering the attitudes of professionals toward adopting new interventions can facilitate implementation [67]. Therefore, we will administer the Evidence-Based Practice Attitude Scale (EBPAS) developed by Aarons in 2004. This scale consists of four subscales for 15 items that are measured on five-point Likert scales, ranging from 0 (not at all) to 4 (to a very great extent). The EBPAS assesses the extent to which a professional (1) finds the intervention intuitively appealing, (2) would adopt an intervention if required by a supervisor, (3) has a general openness to trying new interventions, and (4) perceives interventions as being of limited clinical value and less important than clinical experience. We will use the Dutch version, for which the factor structure and reliability are comparable to the original version [68].

Furthermore, the organizational culture of the DSCUs will be assessed using a Competing Values Framework (CVF) scale [69]. This involves a questionnaire that consists of 24 items on four-point Likert-type scales, ranging from 1 (not characteristic) to 4 (very characteristic). It aims to provide insight into the cooperation between staff members and the working conditions and characteristics of the DSCU, and it suggests either a dominant culture type, a market type, an adhocracy type, or a hierarchy culture type. We will use a Dutch version of the questionnaire [70].

Both the EBPAS and the CVF scale will also be administered in the process evaluation, and they will be sent digitally to NH staff. Finally, a self-designed paper and pencil questionnaire will be used to assess the opinion of family members regarding the delivered care and degree of communication received with respect to NPS and/or psychotropic drug use.

